#### 2.1.3. Exclusion Criteria

-Pediatric.-Any echocardiographic evidence of structural (chordal or leaflet) mitral valve disease.-Papillary muscle rupture.-Infective endocarditis.

A review of the clinical facilities participating in this investigation suggests that the aggregate sample size will be 630. The patient cohort was derived from the databases of the five participating centers, which were subjected to a rigorous screening process to ascertain their eligibility for integration into the analytical framework (Supplementary Material). A combination of monitoring strategies will be employed to oversee the patients, which may include the dissemination of information by mail to the referring physicians of patients who underwent a procedure at the hospitals, direct observation at the center of the surgical procedure, and follow-up telephone interviews with the healthcare providers where the patients were readmitted due to post-procedural complications. The research team conducted periodic assessments of the actual inclusions in comparison to the pre-specified targets. The implementation of a uniform protocol across all centers enabled the documentation of the number of patients who underwent a range of interventions and who were subjected to echocardiographic and clinical follow-up.

The repository of data encompasses information pertaining to the participation of females and ethnic minorities in scientific investigations, specifically clinical trials. This is important for a number of reasons, including those of a scientific, ethical, and social nature, as well as with a view to ensuring the generalizability of the results of the studies conducted. The TEERMISO consortium is dedicated to achieving scientific objectives while ensuring an equitable recruitment of patients, regardless of gender or ethnicity. A minimum of 30% of the TEERMISO registry participants are women, and 25% are from minority ethnic groups. In order to ensure the appropriate representation of these groups, the recruitment centers must implement two measures. Firstly, the number of females and ethnic minorities chosen and enrolled through the screening and exclusion procedures must be recorded. Secondly, these figures must be overseen by each clinical facility on an annual basis. The criteria for inclusion and exclusion of patients who have undergone technical procedures for secondary mitral regurgitation are outlined in the following section (Table 4).

### 2.2. Trial Design and Endpoints

A schematic representation of the trial design is presented in Figure 1.

#### 2.2.1. Primary

The primary endpoint of this study is the degree of LV remodeling as assessed by the Left Ventricular End-Diastolic Volume Index (LVEDVI) at the 10-year follow-up.

#### 2.2.2. Secondary

A number of secondary endpoints will be subjected to evaluation in the context of the forthcoming trial. The trial will evaluate the primary secondary endpoint, which is all-cause mortality. This endpoint offers supplementary clinical data to the primary physiological endpoint, enabling an evaluation of the overall efficacy of the treatment. Moreover, the subsequent secondary endpoints have been delineated for the trial.

▪Functional Status, Hospitalizations, and Neurocognition.NYHA classification.MACE (death, stroke, worsening heart failure (+1 NYHA Class), CHF hospitalization, mitral valve re-intervention).Angina class.Neurocognitive results.Peak VO2 (assessed by a cardiopulmonary stress test).The rates of patients readmitted within 30 days and the long-term readmission rates for all patients, as well as for those with cardiovascular issues and heart failure, are to be determined. Furthermore, the proportion of days spent outside of the hospital setting during the follow-up period following survival will be determined.LOS for the hospital stay and discharge destination.
▪Physiologic Measures.Echocardiography assessment.Quantification of MR, specifically the effective regurgitant orifice area (ERO).Quantifying mitral valve area.LV size, function, and geometry (including LVEF, LVEDD, LVESD, LVEDVI, LVESVI, and LV sphericity).Assessment of mitral valve and subvalvular structures.LA dimension.RV size and function.MV tethering.Assessing regional wall motion for left ventricular function and viability.Appropriate revascularization.▪Safety.
Incidence of serious adverse events.Reoperation for MR and freedom from reoperation in general.▪Perioperative Measures.Operative time for each procedure. For the standard surgical mitral valve operation, cardiopulmonary bypass (CPB) and cross-clamp time are required.Blood loss and transfusion.▪Quality of Life and Economic Measures.
Change in quality of life (QOL).Minnesota Living with Heart Failure (MLHF) score.SF-12.EuroQoL.Dasi.

### 2.3. Therapeutic Interventions

In order to provide the most accurate and comprehensive assessment of primary and secondary endpoints, two distinct patient subgroups will be examined. The initial cohort will consist of patients who underwent TEE) or S-SMVp in conjunction with coronary revascularization, specifically PCI or CABG. The subsequent cohort will comprise patients who did not receive revascularization [14,15,16,17].

▪Standard Mitral Valve Intervention (S-MVi) (S1 Supplementary Material).•Mitral valve replacement (MVrpl).

MVrpl entails the preservation of the subvalvular apparatus with the objective of preventing LV diameter enlargement over time. The decision as to whether to utilize a preservation technique, prosthetic valve type, and suture positioning is at the discretion of the surgeon. In cases of ischemic cardiomyopathy, CABG is a requisite procedure for revascularization.

Restrictive mitral annuloplasty.

An RMA can be carried out with the use of a complete rigid or semi-rigid annuloplasty ring that has been reduced in size to align with the annulus diameter. Given that patients who receive RMA frequently present with CAD, a CABG procedure may be required to facilitate optimal LV remodeling.

Restrictive mitral annuloplasty plus subvalvular repair.

RMA may be in conjunction with the use of SV-r. Subvalvular Repair allows for the approximation or relocation of papillary muscles that are displaced by post-infarction scar formation. In individuals who have undergone SV-r due to ischemic cardiomyopathy, CABG is a necessary subsequent procedure.

▪Transcatheter Mitral Valve Intervention (TMVi) (S2 Supplementary Material) [21,22,23,24,25,26,27,28,29,30,31,32,33,34].•Transcatheter edge-to-edge repair (TEER).

The TEER intervention entails the convergence of the margins of the anterior and posterior leaflets of the mitral valve, a process known as edge-to-edge repair. In the event that a single MitraClip device is insufficient to achieve the desired reduction in MR, a subsequent implant may be employed to optimize the intervention.

▪Endpoint Definitions and Measurement.•Primary endpoint.

The primary objective of the trial is to evaluate the efficacy of the intervention in terms of left ventricular remodeling. This will be accomplished by quantifying the change in the Left Ventricular End-Diastolic Volume Index (LVESVI) at the time of hospitalization and at regular intervals following the procedural intervention, employing transthoracic echocardiography (TTE).

Secondary endpoints.

The main secondary endpoint is mortality, which will be evaluated based on the total number of deaths from any cause.

In addition to the primary endpoints, the trial has defined the following secondary endpoints:Perioperative management.

The variables to be evaluated are as follows: operative time, cardiopulmonary bypass time, cross-clamp time, blood loss, and transfusions.

○Cardiopulmonary bypass parameters.

Information pertaining to the elapsed time of myocardial ischemia, the duration of cardiopulmonary bypass, and the method of cardiac cardioplegia perfusion (retrograde or antegrade) will be extracted from the dataset.

○Blood loss and transfusions. Supplementary Table S1 [35,36,37]○Reoperation for bleeding. Supplementary Table S1 [35,36,37]

A reoperation to reopen the chest for the management of excessive bleeding is indicated in cases where bleeding persists. A reoperation for bleeding is defined as any subsequent surgical procedure necessitated by the necessity to address excessive bleeding in a patient in whom the sternum was left open during the initial operation. It is essential to recognize that reopening the chest for hemodynamic instability without severe bleeding and for the purpose of puncturing the pericardium or pleura or inserting a chest tube for retained blood syndrome is not regarded as a reoperation for bleeding.

▪Functional Status.•MACE (major adverse cardiac event).

A MACE is specified as an unweighted composite score. It consists of the following components:○Death.○Stroke.○Mitral valve re-intervention.○Worsening heart failure (+1 NYHA Class).○CHF hospitalization.•Reoperation.

All subsequent surgical procedures, including reoperations for MR, will be meticulously documented, and the incidence of reoperation will be evaluated through a rigorous time-to-event analysis.

Peak VO2.

In contrast, functional status will be assessed by measuring maximal oxygen uptake (VO2 peak), which will be determined by conducting cardiopulmonary exercise testing at predefined intervals in patients who do not have any clinical indications that would preclude the performance of exercise testing (e.g., unstable angina or left main disease). A uniform verbal prompting protocol will be employed to encourage all patients to exercise to the point of voluntary exertion. The incorporation of Borg’s CR10 RPE (rate of perceived exertion) will be beneficial in subjects who are unable to achieve an RER (respiratory exchange ratio) of ≥1.0, providing an additional measure of the level of exertion. Accordingly, the rating of perceived exertion (RPE) will be evaluated and documented at two-minute intervals for all subjects using the RPE scale, which ranges from 0 to 10. The RPE scale will be used in all tests conducted as part of this study, and patients will be provided with laminated cards illustrating how to use the scale during these tests. A standardized protocol will be employed for the performance of cardiopulmonary exercise testing, and the results will be evaluated by the cardiologist assuming responsibility for the case at the respective enrolment center.

▪Neurocognition.

The aim of this research is to undertake a comparative analysis of the neurocognitive profiles of the treatment groups, employing a battery of tests to assess their cognitive performance. The tests used in this study include the Hopkins Verbal Learning Test, Trail making Tests A and B, MCG Complex Figures, Boston Naming Test, Digit Span, and Digit Symbol Substitution. Neuropsychologists, whose training was conducted by experienced professionals at each recruitment site, will administer the aforementioned neurocognitive tests. The responsibility for scoring the neurocognitive tests will be borne by the neurologists at each center of enrolment.

▪Hospitalization.•Index hospitalization.

The length of stay for the index hospitalization will be quantified and disaggregated by days spent in the ICU. Furthermore, the discharge location will be recorded.

▪Readmission.

The readmission rate will be calculated for the first 30 days after the procedure and for the entire follow-up time. All admissions will be classified, including those related to cardiovascular disease and HF. For a readmission to be considered heart failure-related, at least two of the following signs and conditions of acute decompensated heart failure must be present:Dyspnea felt related to HF.Administration of vasodilators, intravenous diuretics, or inotropes.Pulmonary capillary wedge pressure (PCWP) or LVEDP > 18 mmHg.On physical assessment, rales may suggest the existence of pulmonary edema or pulmonary vascular congestion. This may be seen on radiographs.

All readmissions will be categorized by the investigating physician and adjudicated by the attending cardiologist.

▪Days Spent Alive and Outside of the Hospital.

To assess the total number of days alive and out of the hospital between treatment groups, a pooled analysis will be performed. Additionally, the proportion of days spent out of the hospital in proportion to the total number of days spent alive following the procedure will be quantitatively evaluated.

▪Physiologic Measures.•Echocardiographic tests.○Mitral regurgitation will be evaluated by measurement of effective regurgitant orifice area (EROA) with both proximal isovelocity surface area (PISA) and quantitative flow methods to establish its existence and degree.○The MV apparatus and valve area will undergo evaluation through the assessment of annular shape and motion, the tethering angle and tenting area, the location and distance of papillary muscle, and the calculation of the mean trans-mitral stenotic gradient utilizing mitral inflow continuous wave Doppler.○The following parameters will be employed to evaluate the LV dimension, geometry, and function: LV size, LVEF (biplane Simpson’s rule), LVEDV index using the biplane volumetric method, LV mass, LV sphericity, radial strain, and twist.○The echocardiographic evaluation will encompass the assessment of several structural parameters, including the dimensions of the left atrium, the length and surface area of the mitral valve tethering, the angle of tethering, and the position and degree of separation of the papillary muscles.○The dimensions and functionality of the right ventricle (RV) will be evaluated through the following indices: tricuspid annular plane systolic excursion (TAPSE), peak systolic velocity, diastolic E and A velocities (as determined by tissue Doppler), and fractional area change.○Doppler flow velocity measurement will be used for the purpose of gauging intracardiac pressures and hemodynamics, with a specific emphasis on pulmonary artery pressures (PAPs) and PCWP.○The regional wall motion (LVEF and viability index) will undergo evaluation at the baseline stage and again one year post-surgery. This will enable an estimation of the extent of viability at the baseline stage and an assessment of the impact of revascularization, if any, to be made.•Suitability of revascularization.

Prior to the surgical procedure, the coronary territories are classified as either suitable or unsuitable for bypass. Following the operation, the status of the bypass is monitored. The regions that receive coronary flow should be identified in the following manner. The following coronary territories will be identified: LAD proximal, LAD distal, proximal diagonal, distal diagonal, proximal circumflex, distal circumflex, distal dominant circumflex, right posterolateral, and right posterior descending. Quality of life.

The objective of this study is to evaluate improvements in quality of life (QOL) from baseline utilizing a comprehensive array of disease-specific instruments. These include the Minnesota Living with Heart Failure (MLHF) score, the disease-specific Duke Activity Status Index (DASI), the Short Form-12 general health status index, and the EuroQol 5-D measures of health state preference, with an emphasis on both individual and societal perspectives.

The Minnesota Living with Heart Failure Questionnaire is a quantitative assessment tool designed to evaluate the impact of heart failure and its management on patients across a range of domains, including physical, psychological, and social functioning. The DASI is a multidimensional questionnaire that assesses the cardiovascular impact of four domains of adult activity, each associated with distinct levels of oxygen uptake: ambulation, personal care, domestic tasks, sexual function, and the pursuit of leisure activities. The SF-12 represents a comprehensive quality-of-life assessment tool encompassing eight distinct dimensions: physical activity, social activity, role/physical, body pain, general mental health, role/emotional, vitality, and general health perception. The SF-12 and the EuroQoL 5-D are both instruments designed to assess health-related quality of life. The EuroQol 5-D is a psychometric instrument that yields a succinct descriptive profile comprising five distinct dimensions. The instrument evaluates five domains: (i) anxiety/depression, (ii) pain/discomfort, (iii) usual activities, (iv) self-care, and (v) mobility. Furthermore, it incorporates an evaluation of the individual’s perception of their own health status.

▪Safety.
•Reoperation.•All reoperations, particularly those for mitral regurgitation, will be recorded. Freedom from reoperation will be evaluated.•Adverse events.

An adverse event (AE), as defined by the International Council for Harmonisation of Technical Requirements for Pharmaceuticals for Human Use (ICH), is any event that occurs during a clinical trial and that results in any of the following: a change in the condition of the study participant; a change in the participant’s status; or a new disease or syndrome that the participant develops. An adverse event must be considered clinically significant. Furthermore, it must occur in a participant who is taking part in the trial, regardless of whether the event is related to the study intervention. A pre-existing pathological state will only be designated as an adverse event if there is a discernible alteration in its character, severity, or degree.

A comparison will be made between the two groups with respect to the occurrence of any adverse effects that are deemed to be significant throughout the period of the experimental trial. The onus for adjudicating all serious and protocol-defined adverse events (AEs) will be borne by the clinical control specialists responsible for overseeing this study at each research center. Adverse events will be documented in accordance with specified safety endpoints. The report will provide detailed information on the incidence and prevalence of serious adverse effects, including the frequency of each adverse occurrence, the incidence rate per patient per annum, and the temporal distribution of adverse events. Moreover, the incidence of patients presenting with each discrete category of serious adverse event will be recorded. Safety metrics will be gathered throughout the duration of the patient follow-up period. Subsequently, the incidence of each event type will be calculated with 95% confidence intervals in alignment with the specified safety endpoints.

○Serious adverse event.

In alignment with the directives set forth by the FDA, an adverse event is classified as serious when it results in death, is life-threatening, causes significant or prolonged disability, requires protracted hospitalization, gives rise to a birth defect or congenital abnormality, or, at the discretion of the investigative team, presents other notable hazards or potential for serious injury to the study enrollees or other individuals. In the opinion of the attending clinician, it may be considered appropriate to categorize an episode that is neither lethal nor life-threatening and does not necessitate hospitalization as a serious adverse event. This is on the grounds that a reasonable medical judgment may exist that such an episode may endanger the patient and necessitate medical or surgical intervention in order to avert one or more of the potential outcomes listed in the definition. The subsequent list provides exemplars of medical episodes that may require medical or surgical attention. Such conditions include bronchospasm necessitating intensive treatment in an emergency department or at home, blood dyscrasias, and convulsions that do not result in the need for in-patient hospitalization.

○Unexpected major adverse events.

An unanticipated major adverse incident is defined as a critical adverse occurrence that does not fall within the parameters set forth in the established clinical trial protocol or is not duly recorded in the documentation provided to the patient for review and signature. In the event of an unexpected serious adverse event, it is mandatory to provide unscheduled notification.

In the course of the follow-up period, the occurrence of any adverse events will be duly recorded. The onus will be incumbent upon the investigating physician to ascertain whether a causal relationship exists between the adverse incident in query and the intervention that has been undertaken. The concept of causality is elucidated in Table 5.

▪Specific Adverse Event Definitions.

A myocardial infarction (MI) is defined as a clinical syndrome characterized by the presence of at least one of the following diagnostic criteria, which collectively indicate myocardial necrosis and are consistent with myocardial ischemia [38]. These criteria include the following:Myocardial infarction.

The presence of elevated cardiac biomarkers (preferentially troponin) with a minimum value exceeding the 99th percentile of the upper reference limit (URL), accompanied by evidence of myocardial ischemia through the demonstration of at least one of the following:○New electrocardiogram (ECG) changes indicative of a new episode of ischemia, such as new ST-T changes or new left bundle branch block (LBBB), may be observed.○Ischemia signs.○An ECG examination has revealed the presence of pathological Q waves.○New evidence of loss of viable myocardium or new regional wall motion abnormalities should be sought.•Peri-CABG myocardial infarction.

In subjects presenting with normal baseline troponin values prior to CABG, elevations in cardiac biomarkers above the 99th percentile URL are indicative of peri-procedural myocardial necrosis. It is customary to consider biomarker elevation exceeding five times the 99th percentile URL, in conjunction with the emergence of new Q waves or a newly diagnosed left bundle branch block (LBBB), the formation of a new graft or native coronary artery occlusion as evidenced by angiography, or imaging findings suggestive of new loss of viable myocardium, as indicative of a CABG-related myocardial infarction.

Peri-percutaneous intervention (PCI) myocardial infarction.

For patients who have been treated with PCI and have normal baseline troponin values, any rises in cardiac biomarkers above the 99th percentile upper reference limit indicate the occurrence of peri-procedural myocardial necrosis. It has been standard practice to define PCI-related MI based on the observation of biomarker elevations greater than threefold the 99th percentile upper reference level. Furthermore, there is a recognized correlation between this subgroup and documented instances of stent thrombosis. A death that is sudden and unexpected, in the absence of any apparent cause, is classified as sudden cardiac death. This can be linked to cardiac arrest and may be followed by symptoms that indicate myocardial ischemia. In cases where this occurs, the death may be triggered by the onset of new ST elevation or new LBBB, as well as the presence of fresh thrombus, as identified by coronary angiography and/or autopsy. In the event of a death occurring before the scheduled blood sample collection or the anticipated appearance of cardiac biomarkers in the blood, the cause of death is deemed to be myocardial infarction.

Cardiac arrhythmias.

The presence of any documented arrhythmia resulting in clinical impairment, including but not limited to hemodynamic impairment, oliguria, presyncope, or syncope, necessitates either hospitalization or a physician visit. Additionally, any arrhythmia that manifests during the course of hospitalization requires the same course of action [33,34].

○The persistence of ventricular arrhythmia necessitates defibrillation or cardioversion.○The persistence of supraventricular arrhythmia necessitates the administration of pharmacotherapy or cardioversion.•Right-sided heart insufficiency.

Persistent right ventricular dysfunction can be identified by a central venous pressure (CVP) exceeding 18 mmHg and a cardiac index below 2.0 L/min/m^2^, provided there is no evidence of elevated left atrial/pulmonary capillary wedge pressure (>18 mmHg), tamponade, ventricular arrhythmias, or pneumothorax. These findings should be considered indicative of persistent right ventricular dysfunction. In some instances, medical intervention may necessitate the implantation of a right ventricular assist device (RVAD), the administration of inhaled nitric oxide, or inotropic therapy for a period exceeding seven days [33].

Major infection.

The emergence of a novel episode of clinical infection, characterized by the presence of pain, elevated fever, purulent drainage, and/or an increased white blood cell count, within the context of antimicrobial therapy (non-prophylactic). In cases where infection is present, a culture from the affected site or organ should yield positive results unless there is compelling clinical evidence indicating that treatment is necessary despite negative cultures. Infection may be categorized in a number of ways, as outlined below [32].

○Localized infection.

Infection is confined to a discrete organ or region, such as mediastinitis, with no evidence of systemic involvement, as defined by the presence of sepsis. Such a determination may be made through the utilization of standard clinical methods and may be associated with evidence of a bacterial, viral, fungal, or protozoal infection or may necessitate the implementation of empirical treatment [32].

○Endocarditis.

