## Abstract

**Background:** Secondary mitral regurgitation (SMR) is characterized by a pathological process impacting the left ventricle (LV) as opposed to the mitral valve (MV). In the absence of structural alterations to the MV, the expansion of the LV or impairment of the papillary muscles (PMs) may ensue. A number of technical procedures are accessible for the purpose of determining the optimal resolution for MR. Nevertheless, there is a dearth of rigorous data to facilitate a comparative analysis of MV replacement, MV repair (including subvalvular repair), and transcatheter mitral valve interventions (TMV-Is). The objective of this investigation is to evaluate and compare the efficacy and clinical outcomes of transcatheter mitral valve repair (TMV-r) utilizing the edge-to-edge mitral valve repair (TEER) procedure in comparison to conventional surgical mitral valve interventions (S-SMVis) in patients with secondary mitral regurgitation. **Methods and analysis:** A consortium of five cardiac surgery institutions from four European states and Japan have joined forces to establish a multicenter observational registry, designated TEERMISO. Patients who underwent technical procedures for SMR between January 2007 and December 2023 will be enrolled consecutively into the TEERMISO registry. The investigation team evaluated the comparative efficacy of replacement and repair techniques, utilizing both the standard surgical methodology and the transcatheter intervention. The primary clinical outcome will be the degree of left ventricular remodeling, as assessed by the left ventricular end-diastolic volume index, at 10 years. The forthcoming research will assess a variety of secondary endpoints, among which all-cause mortality will be the primary endpoint. Subsequent assessments will be made in the following order: functional status, hospitalization, neurocognition, physiological measures (echocardiographic assessment), occurrence of adverse clinical incidents, and reoperation. **Ethics and dissemination:** The multicenter design of the database is anticipated to reduce the potential for bias associated with institutional caseload and surgical experience. All participating centers possess an established mitral valve protocol that facilitates comprehensive follow-up and management of any delayed mitral complications following replacement surgery or surgical repair of the secondary mitral regurgitation. The data collected will provide insights into the impact of diverse surgical approaches on standard mitral valve surgery and TEER. This will facilitate the evaluation of LV remodeling over the course of long-term post-procedural follow-up. **Trial Registration:** ClinicalTrials.gov ID: NCT05090540; IRB ID: 202201143

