## 3. Statistical Methods

The presentation of continuous variables will adhere to the prescribed statistical methodology, as delineated in the relevant sections of this study. The reported variables will comprise either the mean and standard deviation or the median and interquartile range, as required. With regard to dichotomous and nominal variables, the resulting data will be presented in the form of a tally and the corresponding percentage. A range of statistical tests will be employed in the univariate analysis, including the Mann–Whitney U-test, Student’s *t*-test, Kruskal–Wallis test, Wilcoxon test, Fisher exact test, Chi-square test, and Kaplan–Meier test. In the event of incomplete datasets, no attempts will be made to supplement the information in question.

Multivariable analyses will be conducted employing the logistic regression model and the Cox proportional hazards model. The variables to be included in the logistic regression analysis will be selected using the Lasso-based variable selection method. Any noteworthy inconsistencies between the study groups will be addressed through the application of propensity score weighting. To estimate the causal effect of exposure on outcomes, a doubly robust approach will be employed comprising combination regression with inverse probability treatment weighting (IPTW) by propensity score. Multivariable analyses will be conducted by employing the logistic regression model and the Cox proportional hazards model. The variables to be included in the logistic regression analysis will be selected using the Lasso-based variable selection method. Any noteworthy inconsistencies between the study groups will be addressed through the application of propensity score weighting. To estimate the causal effect of exposure on outcomes, a doubly robust approach will be employed comprising combination regression with inverse probability treatment weighting (IPTW) by propensity score. In order to accomplish this, a propensity score that balances for covariates will be developed with the objective of minimizing discrepancies between the groups in question.

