A total sample population of 630 patients was calculated as sufficient to detect a significant difference in the rate of reverse left ventricular remodeling, with 384 patients undergoing surgical mitral valve repair and 246 patients undergoing transcatheter mitral valve repair. This study was powered at 80% with a two-tailed alpha level of 0.05. In order for a *p*-value to be deemed statistically significant, it must be less than 0.05. All statistical analyses were performed with the aid of the R software package developed by the R Foundation for Statistical Computing in Vienna, Austria.

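### The primary endpoint is stated inconsistently, and the 80% power for 630 patients cannot be attributed to the declared endpoint, LVEDVI at 10 years

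*Protocol article*

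**What the plan says.** The article describes the primary endpoint or its power basis in four places.

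- **Abstract:** remodeling "as assessed by the left ventricular end-diastolic volume index, at 10 years".
- **Section 2.2.1 (Primary):** "the degree of LV remodeling as assessed by the Left Ventricular End-Diastolic Volume Index (LVEDVI) at the 10-year follow-up".
- **Section 2.3 (Endpoint Definitions and Measurement, Primary endpoint):** the objective is met by "quantifying the change in the Left Ventricular End-Diastolic Volume Index (LVESVI) at the time of hospitalization and at regular intervals following the procedural intervention", using transthoracic echocardiography. The intervals are not listed and 10 years is not mentioned.
- **Section 3 (sample size):** "A total sample population of 630 patients was calculated as sufficient", more fully "sufficient to detect a significant difference in the rate of reverse left ventricular remodeling". The split is 384 surgical and 246 transcatheter patients, with 80% power and two-sided alpha 0.05.

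Three other places bear on the reading. Section 2.2.2 lists "LVEDVI, LVESVI, and LV sphericity" side by side, so the end-diastolic and end-systolic indices are separate measures in this study. The echocardiography list in Section 2.3 specifies "LVEDV index using the biplane volumetric method". For multivariable analysis, Section 3 names "the logistic regression model and the Cox proportional hazards model".

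**The concern.** A primary endpoint needs one variable, one analysis time and one summary measure, and the power statement has to refer to that quantity. Here the written-out name and the abbreviation in Section 2.3 point to different volumes. The analysis time appears in two of the four places only. The sample size rests on a quantity that no other section defines or links to LVEDVI at 10 years.

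Two things are at stake. First, a reader cannot tell what difference the study is powered to detect on its declared endpoint. Second, the analysis is a non-randomised comparison of patients drawn from existing center databases. It is easier to defend if the primary variable is fixed unambiguously in the published plan.

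**Working it through.** **Step 1. The statements side by side**

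| Place | Index | Time | Summary measure |
|---|---|---|---|
| Abstract | end-diastolic | 10 years | degree of remodeling |
| 2.2.1 | LVEDVI | 10 years | degree of remodeling |
| 2.3 | end-diastolic in words, LVESVI in brackets | hospitalization and unlisted intervals | change |
| 3 | none named | none named | rate of reverse remodeling |

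The first two rows agree. The third has a naming error and omits the time point. The fourth shares no stated element with the first two beyond the word remodeling.

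**Step 2. The plan's own figure**

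384 + 246 = 630, so the total adds up. The calculation behind it cannot be reproduced under either a means or a proportions formula, because no effect size, SD or responder rate is stated. A condensed article may leave these inputs to the full protocol, so their absence is not counted as a fault. The calculation is instead run backwards from 384 and 246.

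**Step 3. If the endpoint is a continuous index**

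Detectable standardized difference = (z for two-sided 0.05 + z for 80% power) × √(1/n₁ + 1/n₂)
= (1.960 + 0.842) × √(1/384 + 1/246)
= 2.802 × 0.0817
= **0.229 SD**.

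**Step 4. If the endpoint is a proportion**

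Pooled-variance normal approximation for two proportions, same group sizes, alpha and power. The reference rates are assumptions.

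| Assumed reference rate | Detectable rate | Difference (points) |
|---|---|---|
| 10% | 17.8% | 7.8 |
| 20% | 29.8% | 9.8 |
| 30% | 40.9% | 10.9 |
| 40% | 51.4% | 11.4 |
| 50% | 61.4% | 11.4 |
| 60% | 70.9% | 10.9 |
| 70% | 79.9% | 9.9 |

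**Step 5. Are these the same target?**

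Take a true shift of 0.229 SD in a normally distributed index and analyse it as a responder rate. With an assumed cut giving 30% responders in one group, the other group has 38.4%, and power is about 59%. With a cut giving 50%, the other group has 59.0%, and power is about 60%. A study sized at 80% for one form is not sized at 80% for the other.

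**Step 6. Dependence on the time point**

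Only patients with a 10-year echocardiogram contribute to the declared endpoint. Section 4.1 mentions a 50% mortality rate without a time horizon, so the share below is an assumption, shown over a range and applied equally to both groups.

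| Share with a 10-year echo | Detectable difference | Power for 0.229 SD |
|---|---|---|
| 100% (384 vs 246) | 0.229 SD | 80% |
| 80% | 0.256 SD | 71% |
| 50% (192 vs 123) | 0.324 SD | 51% |
| 30% | 0.418 SD | 34% |

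**The case against.** Much of the discrepancy can be read charitably.

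- **Index.** The end-diastolic index is written out in the Abstract and in Sections 2.2.1 and 2.3, and it is the index in the echocardiography list. LVESVI is attached to the primary endpoint once, in brackets. It is most likely a wrong abbreviation. A reader might infer a rival end-systolic primary endpoint, but the documents do not support that. The slip still needs correcting because LVESVI is a separate measure in Section 2.2.2.
- **Level or change.** Degree of remodeling can naturally mean a change, so Sections 2.2.1 and 2.3 need not conflict here.
- **Time.** The regular intervals can be the echocardiography schedule, with 10 years as the analysis time. Section 2.3 names no competing time point, and Section 4.1 again refers to a 10-year timeframe.
- **Rate.** A reader might infer that Section 3 powers a binary responder endpoint. The text does not say so: the word could mean a proportion, a speed or, loosely, an extent. The methods do not settle it, since Section 3 lists the t-test and Mann–Whitney test as well as logistic regression.

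These readings remove most of the apparent conflict over index, level and time. They do not repair the sample-size sentence: under every meaning of rate, Section 3 fails to tie its power to LVEDVI at 10 years.

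**Conclusion.** The point holds as an internal inconsistency in the primary endpoint and its power basis. Section 2.3 contains an abbreviation error and omits the 10-year time point. Section 3 states power for an undefined quantity, so the 80% figure cannot be attributed to the declared primary endpoint.

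The size of the ambiguity is the gap between the two targets: about 0.23 SD for a continuous index, against about 11 percentage points for a rate. The second figure assumes a reference rate of 30% to 50%. Both assume that all 630 patients contribute a value; the losses in Step 6 are illustrative.

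A reader might go further and infer three mutually incompatible endpoints, or a quantifiable rise in false-positive risk from choosing among them. The documents support neither. Most of the differences have a plausible common reading, and nothing shows that several versions would be tested or that one would be selected after the data are seen.

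**What to change.** 1. In Section 2.3, correct the bracketed abbreviation to LVEDVI and keep LVESVI as secondary.
2. State one primary variable identically in the Abstract and in Sections 2.2.1, 2.3 and 3. Most consistent with the present text is the change in LVEDVI from the pre-procedure echocardiogram to 10 years, by the biplane method already named, with interim echocardiograms as supportive.
3. Restate the sample-size sentence as the LVEDVI difference detectable with 384 against 246 patients, allowing for the proportion expected to have a 10-year echocardiogram.
4. Name an adjusted linear model, weighted by inverse probability of treatment, for this variable. Section 3 plans regression combined with such weighting, but the only multivariable models it names are logistic and Cox, and neither suits a continuous index.
5. Make any responder rate secondary, with a stated threshold.

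The cost is wording in four places, one named model and a new power calculation. That calculation needs an SD for LVEDVI change and an expected 10-year echocardiogram rate, neither of which the article gives. No new data collection is needed. These edits do not settle how deaths before 10 years enter the primary analysis, which should be stated alongside the variable.
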